### Study population/sample size

A sample size calculation was performed based on randomisation with stratification. Using an alpha level of 0.05, a power of 0.8, and an effect size estimates of 1.01 for KAM based on a previous gait retraining study with a similar design compared to our primary comparison (gait pattern group vs control group) [22]. Given that the comparison between gait pattern group and knee moment group is a secondary objective and no study has done the similar design, we will stick with the sample size needed for our primary objective. Seventeen participants are required for each experimental group. Thus, a total of thirty-four participants are needed to adequately power the study and detect significant differences in KAM between groups. Using a conservative estimate of twenty percent drop-out rate, the aim is to recruit twenty participants per group. For control group, we used an allocation ratio of 2:1 requiring recruitment of ten participants. This unequal allocation ratio for control group has been shown to increase the amount of data in the intervention groups where individual responses are likely more variable [30, 31]. In total, this study will recruit fifty participants.

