### Randomisation

After the baseline assessment, participants will be randomly allocated (2:2:1) to the knee moment biofeedback group, gait pattern biofeedback group or control group, using a block randomisation plan by the researcher. Blinding is not achievable in this intervention study, and therefore neither participants nor researcher will be blinded.

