### Statistical analysis

Study outcomes will be assessed quantitatively. The primary outcome will be KAM and KAM impulse, while NRS pain and WOMAC scores will be considered secondary. All other biomechanical outcomes (e.g. spee, EMG data, gait pattern variables) will become exploratory outcome variables in nature. The primary success of the trial will be based on a comparison of KAM reduction between week 0 and week 6, while the success of retention will be based on a comparison of between week 0 and week 10. In the knee moment feedback group, gait pattern changes (FPA, step width and step length) from week 1 to week 6 and 1-month follow-up will be compared to explore the evolvement of the gait pattern in response to knee moment feedback intervention. The proportion of participants adequately completing the programme and the average number of training sessions completed will be reported.

All outcomes will be analysed using the intention-to-treat approach and thus we will include data from all enrolled participants, regardless of dropout. Descriptive statistics will be used to compare participants randomised into the two intervention groups and a control group with respect to baseline variables. Continuous variables will be expressed as the means and standard deviations (if normally distributed). The data normality and sphericity will be tested using Shapiro–Wilk test and Mauchly’s test respectively. Linear mixed effect (LME) models will be used to evaluate whether knee loading variables, knee pain score and WOMAC score significantly differ between the three time points (week 0, week 6 and week 10), with group as fixed effect, and participant (repeat measures) as a random effect. LME will be used for our primary objective to explore the difference between baseline assessment (week 0) and post-intervention assessment (week 6) with comparison of gait pattern group and control group, and the secondary objective to explore the gait pattern difference across all time points in knee moment group. The example LME formula for comparison between the gait pattern and control group within MATLAB is stated as below:$${\text{glme}}\_\mathrm{KAM }=\mathrm{ fitglme}({\text{data}},\mathrm{ ^{\prime}}{\text{KAM}}1 \sim \mathrm{ Group }+\mathrm{ timepoint }+\mathrm{ timepoint}*\mathrm{Group }+ (1|{\text{Participant}})\mathrm{^{\prime}},\mathrm{ ^{\prime}}\mathrm{FitMethod^{\prime}},\mathrm{^{\prime}}\mathrm{Laplace^{\prime}})$$

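### The three-visit mixed model has only a participant intercept, so the week 0 v week 10 retention test can have a wrong standard error, in either direction.

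*Protocol article*

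**What the plan says.** All of the following is in the protocol article.

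- **Three-visit model (Statistical analysis).** Linear mixed models are to show whether knee loading, pain and WOMAC "significantly differ between the three time points (week 0, week 6 and week 10"). The only effects that the sentence then names for this model are these: "with group as fixed effect, and participant (repeat measures) as a random effect". No random slope and no residual covariance structure is named.
- **Written formula (same section).** The one formula given is labelled an example. Its random part is a participant intercept, and its time points are defined as baseline and post-training only.
- **Success criteria (same section).** For the primary result, "The primary success of the trial will be based on a comparison of KAM reduction between week 0 and week 6". For the one-month follow-up, the plan adds that "the success of retention will be based on a comparison of between week 0 and week 10". No separate model is written for retention.
- **Sphericity (same section).** Mauchly's test is planned, with no action attached to its result.
- **Who is seen at week 10 (Overview of the programme).** Only the two intervention groups attend, and no training is given between weeks 6 and 10. The Biomechanical outcomes section speaks more loosely of all groups and of week 9. I follow the Overview, whose seven control visits leave no room for a follow-up.

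**The concern.** With three visits there are three pairwise differences (0–6, 6–10, 0–10). A model whose only random term is a participant intercept uses one pooled residual variance for all of them. This is right only if the three differences have the same variance. The visits are 6 and 4 weeks apart, training lies between the first two and none between the last two, so there is no particular reason to expect equality.

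Retention is a declared success criterion. With no control measurement at week 10, it rests on within-person change in the intervention groups (or on comparing that change between them), so the within-person standard error carries the conclusion. If that error is too small, retention is claimed too readily; if too large, real retention may be missed. Mauchly's test looks at exactly this assumption, yet the plan does not say what happens if it fails.

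**Working it through.** **1. Arm sizes.** The plan states no figure on this point, but its sample size sets the scale. "Using an alpha level of 0.05, a power of 0.8, and an effect size estimates of 1.01 for KAM" leads to "Seventeen participants are required for each experimental group". The normal approximation, n = 2(1.960 + 0.842)² / 1.01² = 15.4, gives 16. The two-sided noncentral t gives power 0.789 at 16 and 0.815 at 17, so 17 is reproduced (sidedness is not stated; two-sided is my assumption). "Using a conservative estimate of twenty percent drop-out rate, the aim is to recruit twenty participants per group", and "participants will be randomly allocated (2:2:1) to the knee moment biofeedback group, gait pattern biofeedback group or control group". So there are 20/20/10 recruited and, at 20% dropout, 20 × 0.8 = 16, 16 and 8 completers.

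**2. Formula.** Take equal variances and let r(a,b) be the correlation between weeks a and b. The variance of a difference is proportional to 1 − r. With complete data, the intercept-only model replaces each pair's value by the mean of the three. Hence, for week 0 v week 10:

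- SE ratio (true / model) = √[(1 − r(0,10)) / mean of the three (1 − r)]
- actual two-sided alpha = 2 × [1 − Φ(1.96 / ratio)]

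**3. Worked examples, one in each direction (correlations assumed).**

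- Decay, r(0,6) = r(6,10) = 0.80 and r(0,10) = 0.64: mean = (0.20 + 0.20 + 0.36)/3 = 0.2533; ratio = √(0.36/0.2533) = 1.19; alpha = 0.100.
- Return towards baseline, r(0,6) = r(6,10) = 0.70 and r(0,10) = 0.80: mean = (0.30 + 0.30 + 0.20)/3 = 0.2667; ratio = √(0.20/0.2667) = 0.87; alpha = 0.024.

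**4. Range over assumed patterns, week 0 v week 10.**

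| Pattern | r(0,6) / r(0,10) / r(6,10) | SE ratio | Alpha |
|---|---|---|---|
| Equal | .80 / .80 / .80 | 1.00 | 0.050 |
| Decay with elapsed time, high correlation | .94 / .90 / .96 | 1.22 | 0.107 |
| Decay with elapsed time, low correlation | .49 / .30 / .62 | 1.15 | 0.087 |
| Decay plus 5% measurement noise | .83 / .76 / .87 | 1.16 | 0.090 |
| Decay plus 15% measurement noise | .74 / .68 / .78 | 1.10 | 0.074 |
| Mild decay | .80 / .75 / .80 | 1.07 | 0.068 |
| Post-training visits alike | .70 / .70 / .85 | 1.10 | 0.074 |
| Return towards baseline | .70 / .80 / .70 | 0.87 | 0.024 |
| Stronger return | .70 / .85 / .75 | 0.80 | 0.015 |

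As correlations approach 1 under decay with elapsed time, the variances go as 6, 4 and 10 weeks (mean 20/3). The ratio tends to √(10 / 6.67) = 1.22 and alpha to 0.11. More exactly, alpha is nominal whenever 1 − r(0,10) equals the mean of the three; equal correlation is the case that the model assumes.

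**5. Simulation check.** With 40,000 trials per pattern, 16/16/8 completers, controls at weeks 0 and 6 only and a REML fit, the within-arm week 0 v week 10 test rejects in 10.5% for .80/.64/.80, 2.3% for .70/.80/.70 and 1.4% for .70/.85/.75. The contrast of change between the two feedback arms behaves almost identically (10.5%, 2.4%, 1.4%).

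**6. Two visits only.** With a single pair of visits there is nothing to average over. A week 0 and week 10 fit by REML rejects in 5.2–5.7% in every pattern. The primary week 0 v week 6 comparison, fitted with two visits by REML, gives 5.5–5.9%. Maximum likelihood adds a little to the week 0 v week 10 fit (6.0–6.4%); that is a small-sample effect, separate from this point.

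**The case against.** Three arguments have weight.

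*The model may not be fixed.* The only formula is an example for two visits, and an article may leave covariance structure to a fuller document. Applied to weeks 0 and 10, that template would have no such problem. This stands in part: the model for retention is not written out. But the example compares the gait pattern group with controls, who have no week 10 visit, so it is not a retention model as it stands. The only sentence covering week 10 for these outcomes is the three-visit one, and it does name its random effect.

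*The assumption is to be tested.* Mauchly's test is planned. That is true, but without a consequence it protects nothing.

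*The direction is unknown.* This stands fully. A reader might infer that the week 0 v week 10 standard error must be too small, that the error rate is about doubled and that retention will be declared too easily, because week 0 to week 10 is the longest gap. The documents do not support that. They give no correlations, and doubling needs strong decay with little visit-level noise. Training stops at week 6, so a drift back towards baseline is a live possibility. Week 6 would then be the odd visit out and the test conservative.

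**Conclusion.** The point holds as a misfit between the three-visit model and the retention contrast, with no fixed direction. Under equal variances and the assumed correlations above, the actual alpha of the nominal 5% week 0 v week 10 test lies between about 0.015 and 0.11, with milder decay patterns at about 0.07 to 0.09. None of these correlations comes from the article.

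The primary week 0 v week 6 KAM comparison, as its two-visit formula is written, is untouched. Nor should a reader infer that the week 0 v week 6 results for pain and WOMAC from a three-visit fit are necessarily conservative. In arms with all three visits, the same formula gives alpha 0.027 for that contrast under .80/.64/.80 but 0.084 under .70/.85/.75, and neither figure was derived for gait pattern v control, where controls have two visits.

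The change is worth making because retention is a declared success criterion and the remedy works whichever way the correlations run.

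**What to change.** State the retention model explicitly, in one of two ways:

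- estimate week 0 v week 10 in its own two-visit model in the intervention groups, in the form already written for week 0 v week 6; or
- keep all three visits and use an unstructured within-person covariance.

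In either case, fit by REML with small-sample degrees of freedom. With either choice Mauchly's test is no longer needed for these contrasts; if it is kept, say what follows from its result.

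The cost is analysis wording, a few more covariance parameters and fewer error degrees of freedom. For two arms of 20 these fall from (40 − 2) × 2 = 76 to 38, which moves the two-sided 5% critical value only from 1.99 to 2.02. For 16 completers per arm they fall from 60 to 30 (2.00 to 2.04). The two-visit option also gives up the week 6 information on participants who miss week 10; the unstructured model keeps it.

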## Abstract

**Background:**

Gait retraining is a common therapeutic intervention that can alter gait characteristics to reduce knee loading in knee osteoarthritis populations. It can be enhanced when combined with biofeedback that provides real-time information about the users’ gait, either directly (i.e. knee moment feedback) or indirectly (i.e. gait pattern feedback). However, it is unknown which types of biofeedback are more effective at reducing knee loading, and also how the changes in gait affect pain during different activities of daily living. Therefore, this study aims to evaluate the acute (6 weeks of training) and chronic (1 month post training) effects of biofeedback based on personalised gait patterns to reduce knee loading and pain in people with knee osteoarthritis, as well as examine if more than one session of knee moment feedback is needed to optimise the gait patterns.

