Gait retraining has been used as an effective, non-invasive strategy to slow down the progression of KOA by reducing the magnitude of knee loading [10]. Previous studies have reported the benefits of a smaller foot progression angle (FPA) for reducing the first peak KAM in both healthy and KOA populations [11, 12]. Greater step widths have been shown to reduce both first and second peak KAMs during walking and stair climbing by reducing the frontal plane ground reaction force moment arm length [13–16]. Finally, smaller step lengths have been found to reduce the peak KAM and KAM impulse in healthy weight and obese adults and KOA population [17–19]. Due to the complexity of walking and various anatomical differences between people, reducing knee loading using a fixed FPA is unlikely to be achievable, and thus a combination of FPA, step width and step length would likely facilitate a personalised gait modification that is comfortable and effective at reducing knee loading [20].

To enhance the performance and learning effect of gait retraining, biofeedback has been employed to provide real-time body information using visual and haptic interfaces [10, 21–23]. By interacting with the live feedback through changes in body position, participants learn how to modify and control their body movement during a motor task, which is gradually internalised over time [24]. Biofeedback is generally employed in two forms; direct feedback provides information about the target outcome itself, in this case knee loading, which participants need to reduce; while indirect feedback provides information about other outcomes such as FPA, step width and step length, which could affect the desired target outcome (i.e. knee loading). Direct feedback has been found to have a better effect on skill learning and retention compared to indirect feedback [25, 26]. however, previous evidence was based on healthy participants [23, 27], and no experimental study has compared different types of feedback in parallel. In addition, while knee loading may be the most effective feedback method in research, it is currently impossible to provide this type of feedback outside a lab setting. Therefore, it is important to explore the effectiveness of indirect feedback (gait pattern) methods that are more feasible in a day-to-day clinical and home settings.

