This study will primarily explore the effectiveness of gait pattern feedback to reduce knee loading and knee pain during a 6-week gait retraining programme, and knee moment feedback group will be exploratory to identify the number of sessions needed to determine the optimal gait pattern over 6 weeks. In a long-term gait retraining programme, the gait patterns identified in the first session may not be optimal due to familiarisation with the environment, skin markers and desired gait alterations, as well as any learning effect or muscle activation adaptations [28]. Therefore, this study will explore if a participant’s optimal gait pattern changes or improves over time when provided with direct knee moment feedback, and how many sessions are required to identify a stable optimised gait pattern. Furthermore, there have not been any studies exploring the translative effect of gait retraining intervention into daily activities other than walking (e.g. sit-to-stand or stair climbing). Addressing these knowledge gaps in the literature will produce quantifiable outcome measures to identify and support the implementation of gait retraining for future clinical rehabilitation in KOA populations.

The primary objective of this study is to compare the effectiveness of gait pattern feedback to a control group, during a 6-week gait retraining programme in a KOA population. The secondary objectives are as follow:Explore the evolvement of gait patterns (FPA, step width and step length) when using knee moment biofeedback over time.Determine the optimal number of knee moment biofeedback sessions to identify the best combination of gait patterns (FPA, step width, step length) and quantify individual differences in the timescale for adaptation.Compare the similarity between gait pattern feedback and knee moment feedback to reduce KAM and pain.Explore and compare the successful internalisation of these two types of biofeedback gait retraining over time, through dual tasks, muscle activation and one-month gait retention.Explore the translative effect of these biofeedback gait retraining programmes on general daily activities.

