## Conclusion

To the best of our knowledge, this is the first study to explore the effectiveness of gait pattern biofeedback gait retraining on knee loading and knee pain in KOA population, compared to a control group. The results of this study will also identify the number of sessions needed to identify the optimal gait pattern using knee moment feedback. The similarity of effectiveness between gait pattern and knee moment feedback will be assessed as exploratory objective. The results can provide guidance of clinical implementation and further progress the development of portable gait retraining devices for use outside of the laboratory. This study will also explore the muscle activation alterations during gait retraining sessions, which can help illuminate the potential effective mechanisms of gait retraining. Furthermore, this study aims to close the knowledge gap in the literature on the translative effect of gait retraining on other daily activities, such as stair climbing and sit-to-stand. A comprehensive and effective gait retraining programme may represent a practical and self-administered approach to slow KOA progression and improve quality of life in patients with knee osteoarthritis.

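### The mixed model stated for the knee moment arm describes average change from week 1 and does not answer how many feedback sessions a person needs

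*Protocol article*

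**What the plan says.** **What is promised.** The secondary objectives in the Background section of the protocol article list two separate aims for knee moment feedback. One is descriptive: "Explore the evolvement of gait patterns (FPA, step width and step length) when using knee moment biofeedback over time". The other is a count with an individual-level part: "Determine the optimal number of knee moment biofeedback sessions to identify the best combination of gait patterns", and "quantify individual differences in the timescale for adaptation". The abstract frames the same question as whether to "examine if more than one session of knee moment feedback is needed to optimise the gait patterns", and the Conclusion states the answer as an expected result: "The results of this study will also identify the number of sessions needed to identify the optimal gait pattern using knee moment feedback".

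**What is analysed.** The Statistical analysis section gives one longitudinal comparison for this arm: "gait pattern changes (FPA, step width and step length) from week 1 to week 6 and 1-month follow-up will be compared". It ties that comparison to the evolution of the pattern. Later in the section it says that a linear mixed model will serve "the secondary objective to explore the gait pattern difference across all time points in knee moment group". Participant is the only random effect named. The printed example formula is for gait pattern versus control.

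**When the sessions occur.** Under Biofeedback identification session, both intervention groups receive knee moment feedback at week 0b, and a five-minute exploration is recorded to find each person's best pattern. Weekly training follows in weeks 1 to 6. Under Gait pattern biofeedback gait retraining group, that arm's targets come from week 0b and stay the same throughout.

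**The concern.** The session-count aim is about individuals: when each person's pattern settles, and how that differs between people. The stated analysis is about averages. A time effect in a mixed model shows that the mean moved between some sessions; it gives neither a number of sessions per person nor a distribution of adaptation times.

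The window matters for a second reason. The question of whether more than one session is needed is a question about the first session, which is week 0b. That session also sets the gait pattern arm's fixed targets, so whether one session is enough bears on how good those targets are.

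At stake is an answer announced in the abstract, the Discussion and the Conclusion. Without a matching analysis, a session number would have to be read informally from an average curve.

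**Working it through.** **The plan's own figure.** The article gives no calculation for the session count. Its only computed figure is 17 per group for the primary KAM comparison. A two-sided two-sample t-test with alpha 0.05, power 0.8 and effect size 1.01 gives 16.41, rounded up to 17. It reproduces but has no bearing on this objective.

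**1. Averages do not identify timing.** Take 20 people, each with a total change of 1 unit between weeks 1 and 6. No one moves in the opposite direction.

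| | Wk 1 | Wk 2 | Wk 3 | Wk 4 | Wk 5 | Wk 6 |
|---|---|---|---|---|---|---|
| A: four people jump once at each of weeks 2 to 6, group mean | 0 | 4/20 = 0.2 | 8/20 = 0.4 | 12/20 = 0.6 | 16/20 = 0.8 | 20/20 = 1.0 |
| B: everyone changes gradually, (week − 1)/5 | 0 | 0.2 | 0.4 | 0.6 | 0.8 | 1.0 |
| Share settled, A | 0% | 20% | 40% | 60% | 80% | 100% |
| Share settled, B | 0% | 0% | 0% | 0% | 0% | 100% |

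The mean curves are identical. The median settling week is 4 in A and 6 in B.

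**2. The window.** Knee moment feedback is given at week 0b and then in weeks 1 to 6, so this arm has seven such sessions. A comparison from week 1 can show that patterns kept moving after the second session. If the curve is flat from week 1, it cannot show whether the first session had already found the final pattern, because any change between week 0b and week 1 lies outside it.

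**3. Opposite directions, if they occur.** If a share p moves one way by 5 units and the rest move the other way, the mean signed change is 5(2p − 1), while the mean absolute change is always 5. The following values are assumed and not in the documents: 20 people, weeks 1 to 6, within-person SD 1.5, between-person SD 6, plateau reached at week 2 to 6 with equal chance. The last two columns give the chance that a random-intercept time effect is significant.

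| Share one way | Mean signed change | Exact split | Directions drawn at random |
|---|---|---|---|
| 50% | 0 | 0% | 10% |
| 60% | 1 | 2% | 21% |
| 70% | 2 | 52% | 53% |
| 80% | 3 | 99.7% | 85% |
| 100% | 5 | 100% | 100% |

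With a smaller assumed shift (2 within-person SDs, seven time points), the chances were about 100%, 45% and 9% at shares of 100%, 70% and 50%.

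**4. Why non-significance could not stand in for stability.** A paired contrast has 80% power only for 0.66 SD of the differences with 20 people, or 0.75 SD with 16 (20 × 0.8, the plan's dropout allowance). Suppose everyone drifts steadily by 2 within-person SDs over the seven sessions. Each step is 2/6 = 0.33 within-person SD. With independent errors that is 0.33/√2 = 0.24 SD of the differences, well below 0.66.

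**5. Choice of reference for a per-person rule.** With total steady change S, position at session j is jS/6. The mean of sessions 5 and 6 is (5S/6 + S)/2 = 11S/12, so both sessions lie only S/12 from it. At S = 2 SD that is 0.17 SD, so a person still drifting would look stable against that mean. The direct difference between sessions 5 and 6 is S/6 = 0.33 SD.

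**The case against.** **The mixed model is not said to answer the session count.** This stands. The article links it to the evolution objective, for which it is suitable. The point is that it is the only longitudinal analysis stated for this arm and does not reach the other objective.

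**A stability rule may sit in a fuller plan.** This also stands; its absence from an article is not the finding. But the comparison window is stated here, it leaves out the session that the question is about, and it sits beside looser wording about all time points.

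**Week 0b is a different task.** True: participants vary each parameter in turn and then explore freely, whereas training works towards a set target. That calls for a caveat, not for exclusion.

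**Stronger readings that the text does not support.**
- A reader might infer that personal changes will cancel. The article says "reducing knee loading using a fixed FPA is unlikely to be achievable", which means that one value will not suit everyone, not that directions oppose. The same paragraph of the Background describes common directions: smaller foot progression angle, wider steps, shorter steps. Signed modelling is itself an inference.
- A reader might infer that a p-value above 0.05 between sessions will be taken as stability. No such rule is stated.
- A reader might infer an intercept-only model from the printed formula. That formula is an example for another comparison.

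**The arm is exploratory.** Correct, and it limits the weight of the point.

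**Conclusion.** The point holds in a limited form. The stated model describes average change and does not yield the number of sessions needed or the spread of individual adaptation times. This follows from the algebra alone and needs no assumption about direction or shift size. The explicit window omits the first knee moment session and conflicts with the looser wording in the same section.

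Hidden change through opposite movements is a possibility only. On the assumed values it matters when directions are close to evenly split and largely disappears when most people move the same way.

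The primary comparison of KAM between the gait pattern and control groups is unaffected. What is affected is whether the exploratory arm can deliver its announced result.

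**What to change.** - Keep the mixed model and label it as a description of how gait patterns evolve.
- State one window. Include the recorded week 0b pattern as the first knee moment session, and note that its task differs from training.
- Pre-specify a per-participant analysis. For foot progression angle, step width, step length and KAM, compute absolute between-session differences, scaled by that person's stride-to-stride SD. Define sessions-to-stability as the first session after which all later between-session differences stay within a pre-set margin.
- Apply the margin to every pair of later sessions, not only adjacent ones, so that slow drift accumulates and is seen.
- Treat participants still changing between the last sessions as censored at session 6. Do not measure distance from a mean of sessions 5 and 6, which presumes stability at the end.
- Report the distribution of sessions-to-stability and the share stable by each session with confidence intervals. Do not infer stability from non-significance.

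**Cost.** Wording and some programming. No new data are needed: the week 0b exploration is recorded, and knee loading and gait pattern data are collected at every training session. The downside is that a margin must be chosen and justified, and stability late in the programme rests on few differences. With 20 people the intervals will be wide and the results remain exploratory.
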